## Abstract

**Background:**

The management of patients with angiographically intermediate coronary lesions is a major clinical issue. Fractional flow reserve provides validated functional insights while optical coherence tomography provides high resolution anatomic imaging. Both techniques may be applied to guide management in case of angiographically intermediate coronary lesions. Moreover, these techniques may be used to optimize the result of percutaneous coronary intervention. We aim to compare the clinical and economic impact of fractional flow reserve versus optical coherence tomography guidance in patients with angiographically intermediate coronary lesions.

**Methods/Design:**

Patients with at least one angiographically intermediate coronary lesion will be randomized (ratio 1:1) to fractional flow reserve or optical coherence tomography guidance. In the fractional flow reserve arm, percutaneous coronary intervention will be performed if fractional flow reserve value is ≤0.80, and will be conducted with the aim of achieving a post-percutaneous coronary intervention fractional flow reserve target value of ≥0.90. In the optical coherence tomography arm, percutaneous coronary intervention will be performed if percentage of area stenosis (AS%) is ≥75% or 50 to 75% with minimal lumen area <2.5 mm^2^, or if a major plaque ulceration is detected. In case of percutaneous coronary intervention, optical coherence tomography will guide the procedure in order to minimize under-expansion, malapposition, and edge dissections.

Cost load and clinical outcome will be prospectively assessed at one and thirteen months. The assessed clinical outcome measures will be: major cardiovascular events and occurrence of significant angina defined as a Seattle Angina Questionnaire score <90 in the angina frequency scale.

**Discussion:**

The FORZA trial will provide useful guidance for the management of patients with coronary artery disease by prospectively assessing the use of two techniques representing the gold standard for functional and anatomical definition of coronary plaques.

**Trial registration:**

Clinicaltrials.gov NCT01824030

## Background

The decision on when and how to treat patients with coronary artery disease represents a major clinical issue and is usually based on a clinical evaluation combined with analysis of coronary angiography. Yet a growing body of evidence suggests that coronary angiography fails to allow detailed assessment of coronary atherosclerotic plaque morphology and severity [1]. As a consequence, in recent years a series of novel technologies have been developed in order to improve the assessment of patients with coronary artery disease [2-4]. Their use may improve the decision making process in patients with equivocal findings at coronary angiography, such as patients with angiographically intermediate coronary lesions (AICL) [1].

The first of these strategies is represented by fractional flow reserve (FFR), defined as the ratio of pressure distal to the stenosis and aortic pressure after induced maximal hyperemia. Its normal value is 1, while a value of 0.75 has been initially purposed as the cutoff in identifying the presence of myocardial ischemia in a validation study of comparison with non-invasive tests, showing a 93% diagnostic accuracy with 100% specificity and an 88% sensitivity [5]. The same cutoff has been confirmed in the DEFER study, in which deferred revascularization of intermediate stenosis was shown to be safe if FFR was above 0.75, with similar long term outcomes in patients in both the percutaneous coronary intervention (PCI) group and those in the defer PCI group [6].

The more conservative cutoff of 0.80 has been tested in two large randomized clinical trials, showing in the drug-eluting stent era, a net clinical and economic advantage from a FFR-guided revascularization strategy [7,8]. On the basis of the FAME [7] and FAME 2 [8] trials, a cutoff value of 0.80 is currently being used in clinical practice in order to identify the ischemic burden associated with AICL, and to guide the choice between revascularization and optimal medical therapy. As shown in Table 1, FFR remains the main technique to be used in clinical studies exploring the impact of adjunctive invasive assessment strategy in guiding the management of patients with AICL.

**Table 1 T1:** Main studies about impact of adjunctive intracoronary techniques to guide PCI in intermediate coronary lesions

**Study**	**Year**	**Patients**	**Technique**	**Lesions**	**Comparison**	**FUP**	**MACE**	**Recurrent Angina**
DEFER [6]	2007	325	FFR	Intermediate Stenosis	FFR guided PCI FFR guided OMT	5 years	↔ in PCI vs OMT (3.3% vs 7.9%, *P* = n.s)	↓ in OMT vs PCI (43.0% vs 33.0%, *P* = 0.02)
Courtis *et al.*[10]	2008	107	FFR	Intermediate Stenosis	FFR guided PCI FFR guided OMT	13 months	↓ in PCI vs OMT (5% vs 23%, *P* = 0.005)	↓ in PCI vs OMT (9.0% vs 41.0%, *P* = 0.002)
Courtis *et al.*[11]	2009	142	FFR	Intermediate Stenosis on LM	FFR guided PCI FFR guided OMT	14 months	↔ in PCI vs OMT (7.0% vs 16.0%, *P* = n.s.)	↓ in PCI vs OMT (20.0% vs 36.0%, *P* = 0.008)
Nam *et al.*[12]	2010	167	FFR vs IVUS	Intermediate Stenosis	FFR guided PCI IVUS guided PCI	1 year	↔ in FFR vs IVUS (3.6% vs 3.2%, *P* = n.s.)	________
Muller *et al.*[13]	2011	730	FFR	Intermediate Stenosis on LAD	FFR guided PCI FFR guided OMT	40 months	↓ in OMT vs PCI (9.7% vs 26.7%, *P* <0.001)	________
Misaka *et al.*[14]	2011	44	FFR	Intermediate Stenosis	FFR guided PCI FFR guided OMT	53 months	↔ in PCI vs OMT (13.3% vs 6.9%, *P* = n.s)	________

FFR, fractional flow reserve; FUP, follow up; IVUS, intravascular ultrasound; LAD, left anterior descending; LM, left main; MACE, major cardiovascular event; MI, myocardial infarction; OMT, optimal medical therapy; PCI, percutaneous coronary intervention.

On the other hand, frequency domain technique optical coherence tomography (FD-OCT), an intracoronary imaging technology warranting quick and precise evaluation of coronary lumen and the vessel wall [4], has entered into clinical practice, providing promising clinical results when applied to guide PCI [9]. On such a basis, most of interventional cardiology centers are (or are going to be) equipped with one or both of the equipment for FFR and FD-OCT. Due to the absence of dedicated trials (Table 1) [6,10-14], the decision of when to use one of these two tools is left to the operator and/or centre preference. Yet, these two techniques have a completely different approach to plaque evaluation, since stenosis-related flow limitation and plaque morphology may influence different aspects of the natural history of ischemic heart disease. Thus, we designed the present prospective clinical trial aimed at comparing the clinical and economic implications associated with the selection of FFR or FD-OCT in the management of patients with AICL.

## Methods/Design

### Study design

The FORZA study is an open label prospective single centre randomized trial comparing the costs and the rate of adverse clinical outcomes in patients randomized to FFR versus FD-OCT guided PCI on AICL.

Consecutive patients with evidence of AICL, defined as a coronary lesion with a visually estimated percentage diameter stenosis ranging from between 30 and 80% [15], will be prospectively enrolled and randomized to FFR guidance or FD-OCT guidance at a ratio of 1:1.

Each patient will complete a Seattle Angina Questionnaire (SAQ) before intervention, at one month, and thirteen months follow up. Details on SAQ are reported in the Methods/Design section. FFR and FD-OCT assessment will be performed at the site of AICL according to technical details reported in the Methods/Design section below. The study flow chart is summarized in Figure 1.

**Figure 1 F1:**
[figure not shown]
**Study flow chart.** (AS%, percentage of area stenosis; FFR, flow fractional reserve; MLA, minimal lumen area; OCT, optical coherence tomography; PCI, percutaneous coronary intervention; SAQ, Seattle angina questionnaire).

The specific inclusion and exclusion criteria for the study are reported in Table 2.

**Table 2 T2:** Inclusion and exclusion criteria

**Inclusion criteria**	**Exclusion criteria**
**Clinical**	**Clinical**
Age >18 years	Age <18 years
Diagnosis of ischemic heart disease	Inability to give informed consent
	Female with child-bearing potential
**Angiographic**	Life expectancy <12 months
Single vessel disease with angiographically intermediate coronary lesion OR	Factors making clinical follow up difficult (such as no fixed address)
Multivessel disease with only angiographically intermediate coronary lesion OR	Poor cardiac function as defined by left ventricular global ejection fraction ≤30%
Multivessel disease with at least one angiographically intermediate coronary lesion and already treated angiographically critical stenosis	Recent (<7 days) ST-segment elevation Myocardial infarction
	Recent (<48 hours) Non ST-segment elevation myocardial infarction
	Prior ST-segment elevation myocardial Infarction in the territory supplied by the vessel with the intermediate under investigation
	Severe myocardial hypertrophy (interventricular septum thickness >15 mm, ECG Sokolow’s criteria fulfilled)
	Severe valvular heart disease
	Significant platelet count alteration (<100,000 cells/mm3 or >700,000 cells/mm^3^)
	Gastrointestinal bleeding requiring surgery or blood transfusions within the four weeks previous
	History of clotting pathology
	Known hypersensitivity to aspirin, heparin, or contrast dye
	Advanced renal failure with a glomerular filtration rate <30 ml/min
	**Angiographic**
	Multivessel disease with one or more untreated angiographically critical stenosis or coronary occlusion.
	Lesions in coronary artery bypass grafts
	Multivessel disease requiring coronary aortic bypass graft intervention

### Study endpoints

The occurrence of significant residual angina (<90 score at SAQ angina frequency scale) at 13 months represents the primary endpoint of the study.

Major cardiovascular events (MACE), defined as the occurrence of death, myocardial infarction (MI) and target vessel revascularization (TVR), will be prospectively assessed. Since the rate of MACE is anticipated to be low, and most of the procedures in patients with AICL are performed with the aim of improving symptoms, the recurrence of significant angina (defined as an SAQ score <90 on the angina frequency scale) will be prospectively assessed as well.

The first secondary endpoint will be the combined endpoint of recurrence of significant angina or MACE at 13 months follow up. However, in the case of a MACE rate absolute difference of >1% between the two study arms, this combined endpoint will be considered as the primary endpoint of the study.

A further secondary endpoint will be the global costs of the strategy (FFR or FD-OCT guided) at one and thirteen months follow up.

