### Sample size calculation for clinical outcome

FFR-based treatment has proven to be superior to standard (based on angiography only) treatment by reducing the occurrence of MACE in the long-term [35]. Yet angina relief (an important determinant of quality of life in patients with ischemic heart disease) was not ameliorated by FFR guidance in a recent trial [7]. Thus, the FORZA trial aims to test if FD-OCT guidance may help to improve the clinical management of patients with ischemic heart disease and inconclusive results at coronary angiography. Since hard clinical endpoints are expected to have low frequency and PCI (especially in patients with good prognosis) is performed with the aim of improving the quality of life by eliminating angina and improving heart function, the occurrence of significant residual angina (<90 score at SAQ angina frequency scale) at 13 months has been considered as the primary endpoint.

For sample size calculations, we focused our attention on the clinical outcome at 13 months (a timepoint chosen assuming that most of patients had completed their 12-month double antiplatelet therapy one month before). Then, based on the FAME trial [7], we anticipate 20% of patients will be suffering from persistent angina at follow up in the FFR guidance group. Thus, 20% of patients are expected to have reached the primary endpoint at 13 months in the FFR guidance group. For the present study, we hypothesize that FD-OCT guidance could be able (due to the treatment of a greater number of stenoses and the optimization of stenting procedures which may reduce the rate of untreated angina-causing lesions) to reduce the occurrence of the primary endpoint by 50%. As a consequence, a total number of 400 patients (200 randomized to FFR guidance and 200 to FD-OCT guidance) has been calculated to be needed with an alpha error of 5% and a beta error of 20%.

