This sample size is also suitable to satisfy the secondary endpoint of the study, represented by a combination of MACE and/or relief from angina at 13-month follow up. Indeed we assume to have a 5% rate of MACE in the FFR guidance group, in line with the rate observed in a previous study of patients with intermediate lesions treated on the basis of FFR [10]. Thus, combined with the 20% of patients suffering persistent angina at follow up in the FFR guidance group, 25% of patients are expected to have reached the secondary endpoint at 13 months in the FFR guidance group. Since we expect a significant reduction in angina but not in MACE occurrence in the FD-OCT patients, we assume a 50% reduction (exclusively due to angina relief) of the secondary endpoint in this group. As a consequence, a total number of 304 (152 randomized to FFR guidance and 152 to FD-OCT guidance) has been calculated to satisfy the secondary endpoint requirements, with an alpha error of 5% and a beta error of 20%.

Finally, since the sample size is strongly dependent on the rate of events observed in the reference group (and figures in the literature are highly variable), when the first 150 patients complete the 13-month follow up, an interim analysis will be performed and eventually an amendment with a novel sample sizing will be calculated in the case of >30% difference between expected and observed rates.

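### An observed between-arm MACE difference of more than 1% decides which endpoint is primary, a threshold inside chance variation; type I error rises slightly and power probably falls

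*Protocol article*

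**What the plan says.** The Study endpoints section of the protocol article fixes the primary endpoint: "The occurrence of significant residual angina (<90 score at SAQ angina frequency scale) at 13 months represents the primary endpoint of the study". It then ranks the composite: "The first secondary endpoint will be the combined endpoint of recurrence of significant angina or MACE at 13 months follow up". The next sentence makes that ranking conditional: "a MACE rate absolute difference of >1% between the two study arms, this combined endpoint will be considered as the primary endpoint".

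The section Sample size calculation for clinical outcome again treats angina as primary ("at 13 months has been considered as the primary endpoint") and sizes the trial on it at 400 patients, 200 per arm, with 5% alpha and 20% beta. It gives a separate figure of 304 patients for the composite, at the same error rates. On MACE it says: "Since we expect a significant reduction in angina but not in MACE occurrence in the FD-OCT patients". The article mentions no alpha adjustment for the switch.

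**The concern.** The selector is neither a pooled nor a blinded event rate. It is the observed difference between the arms in MACE, which is itself part of the endpoint that the rule brings in. The composite is therefore promoted exactly when its MACE part is imbalanced, whichever arm that favours.

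Two things are at stake. First, a test chosen by looking at part of its own outcome need not keep its nominal 5% level. Second, the trial was sized on angina. If the switch fires by chance when MACE does not differ, the composite adds noise without adding effect, and power drops. Both depend on how often the switch fires, so the 1% threshold has to be compared with chance variation at 200 per arm.

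**Working it through.** **Inputs from the article.** 200 per arm. Angina 20% under FFR ("20% of patients are expected to have reached the primary endpoint at 13 months in the FFR guidance group"), with FD-OCT expected "to reduce the occurrence of the primary endpoint by 50"%, so 20% versus 10%. MACE 5% under FFR, with no reduction expected under FD-OCT. Composite 25% under FFR, stated to be halved to 12.5%. Alpha 5%, power 80%.

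**Assumptions.** Two-sided testing is inferred from the reproduction in step 1. The overlap between angina and MACE is not given beyond the sum 20% + 5% = 25%, so three cases are shown: mutually exclusive, independent, and MACE nested in angina. MACE rates of 2% and 8% are added as a range around the planned 5%.

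**1. Reproducing the plan's sample sizes.** Two-sided, pooled variance under the null, no continuity correction:

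n per arm = [1.96·√(2p̄(1−p̄)) + 0.842·√(p₁(1−p₁) + p₂(1−p₂))]² / (p₁−p₂)²

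- 20% vs 10%: (1.96·√0.255 + 0.842·√0.25)² / 0.01 gives 199 per arm, 398 in total (stated 400).
- 25% vs 12.5%: (1.96·√0.3047 + 0.842·√0.2969)² / 0.015625 gives 152 per arm, 304 in total (stated 304).

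Both stated figures are reproduced.

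**2. How often the switch fires by chance.** More than 1% of 200 is more than 2 patients, so a gap of 3 or more. At 5% MACE in both arms, the standard error of the difference is √(2·0.05·0.95/200) = 0.0218, or 2.2 points, about twice the threshold. Summing the product of two binomial distributions over all gaps of 3 or more, with equal true rates:

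| True MACE, both arms | Probability of switching |
|---|---|
| 2% | 36.4% |
| 5% | 56.4% |
| 8% | 64.4% |

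**3. Type I error.** 1,000,000 simulated trials per scenario, pooled z-test at 1.96, angina 20% and MACE 5% in both arms:

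| Overlap | Angina always primary | Switch rule | Composite test among switched trials |
|---|---|---|---|
| Exclusive | 5.0–5.1% | 5.6–5.7% | 6.2% |
| Independent | 5.1% | 5.75% | 6.3% |
| Nested | 5.1% | 5.1% | 6.6% |

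Over MACE rates of 2–8%, with exclusive or independent events, the rule rejects in 5.4–5.9% of null trials.

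**4. Power.** Angina 20% vs 10%, MACE 5% in both arms:

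| Overlap | Angina always primary | Switch rule | Composite test among switched trials |
|---|---|---|---|
| Exclusive | 81.1% | 74.6% | 69.4% |
| Independent | 81.1% | 72.8% | 66.3% |
| Nested | 81.1% | 81.1% | 77.8% |

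The normal formula gives 80.2% for angina at 200 per arm; 81.1% is the simulated value for the same test, so comparisons are made within the simulation. Over MACE rates of 2–8%, with exclusive or independent events, power under the rule is 67–79%.

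**5. Which composite rates follow from the plan.** Halving angina and leaving MACE alone takes 20% + 5% = 25% to 10% + 5% = 15%, not 12.5%. For 25% vs 15%, the formula in step 1 gives (1.96·√0.32 + 0.842·√0.315)² / 0.01 = 250 per arm, 500 in total. Power at 200 per arm is Φ[(√200·0.10 − 1.96·√0.32)/√0.315] = Φ(0.544) = 70.7%. At 25% vs 12.5%, power at 200 per arm would be 89.6%.

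To keep every stated rate at once (angina 20% vs 10%, MACE 5% in both arms, composite 25% vs 12.5%), the two events must never coincide under FFR but must coincide in 2.5% of patients under FD-OCT (10% + 5% − 2.5% = 12.5%). Simulated on that pattern, the rule has about 85% power.

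**The case against.** The strongest reply is that the rule, its threshold and both candidate endpoints are published in advance and both are sized, so this is not a post hoc change. That stands, and the point is not one of hidden switching. But writing a rule down does not make the selector independent of the treatment comparison. An analysis plan not shown here could add an alpha adjustment, but it could not make the primary endpoint fixed while this sentence remains.

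The second reply is that the numerical harm is limited. This also largely stands:

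- The type I excess is about half to three quarters of a point, and it is nil overall if every MACE patient also has angina. The 6.2–6.3% figure applies only to trials that switch and is not the trial's error rate.
- At 2% MACE with exclusive events, power falls by only about 2 points, from 81.1% to 78.9%, and the article itself expects few MACE.
- If FD-OCT truly lowered MACE from 5% to 3% (independent events), power under the rule would rise to 86%. The protocol does not expect that. If FD-OCT raised MACE from 3% to 5%, power would fall to 57%.

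A reader might go further and infer that power falls below 80% on any reading of the planning assumptions. The documents do not support this: on the stated 25% vs 12.5% composite, power rises to about 85%. That figure sits badly with the article's attribution of the whole reduction to angina relief, but it is a stated assumption. A reader might also infer that the sponsor may claim whichever endpoint succeeds. The rule does not allow that, since it designates one endpoint by a fixed threshold.

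**Conclusion.** The concern holds in a limited form. The primary endpoint is selected by an observed between-arm difference in a component of one candidate, at a threshold of about half a standard error. On the planned 5% MACE rate, chance alone decides the matter roughly as a coin toss would (56%).

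The type I cost is modest: 5.6–5.8% against 5.1%. The power cost is larger, about 6 to 8 points, and brings the trial below its planned 80%. It rests on three things: angina 20% vs 10%, MACE 5% in both arms, and events that are exclusive or independent. It disappears if MACE is nested in angina and reverses on the 12.5% composite rate.

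The main defect is that which endpoint is primary depends on the treatment comparison; the half-point or so of alpha is secondary.

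**What to change.** By amendment, before any comparison by arm (including the interim analysis at 150 patients, if arms are compared there):

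- Delete the sentence that promotes the composite when the MACE rates differ by more than 1%.
- Keep angina at 13 months as the only primary endpoint, whatever the MACE result.
- Keep angina-or-MACE as first secondary, for example tested at 5% only if the primary is significant.
- Always report MACE by arm, with a confidence interval for the difference.

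This restores about 5% type I error and about 80% power at the planned 400, with no extra patients or data.

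Fixing the composite as sole primary, or making both co-primary with split alpha, would also remove the data-dependence, but each needs re-sizing. The composite alone would need about 500 patients at 25% vs 15%. If the composite keeps its own sample size statement, the 12.5% rate should be reconciled with the assumption of no MACE reduction.

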### Procedure description

A guiding catheter (shape and size chosen by the operator) will be placed at the coronary ostium. Then, according to randomization, FFR or FD-OCT assessment will be performed as described below. PCI will be performed at the same time or in a second procedure (‘staged procedure’) according to the decision of the operator only if the pre-specified FFR or FD-OCT criteria are fulfilled, otherwise the patient will be discharged on optimal medical treatment as recommended by international guidelines [16]. The decision regarding pre- and post-dilation, and the type and number of stents needed to cover all of the diseased segment will be left to operator’s discretion. Thereafter, FFR or FD-OCT will be performed and further optimization of PCI procedure will be performed as described below.

### FFR guidance

After intravenous administration of heparin 100 IU/kg, a 0.014 inch pressure monitoring guidewire (Pressure Wire Certus, St. Jude Medical, St. Paul, New Mexico, United States) will be calibrated and advanced into the guiding catheter until the pressure transducer will be just outside its tip, allowing equalization of the pressure measured by the sensor on the guidewire with that measured by the guiding catheter. The guidewire will then be advanced beyond the AICL under examination. Special attention will be paid to avoid arterial pressure wave damping, non-selective cannulation of coronary ostia, and variations in the position of the pressure wire tip. FFR will be calculated as the lowest ratio of distal coronary pressure (Pd) divided by aortic pressure (Pa) after achievement of maximal hyperemia, obtained using intravenous or intracoronary adenosine according to our hospital’s internal protocol [17]. The femoral or brachial vein will be used for intravenous administration of 140 μg Kg-1 min-1 adenosine and maximal hyperemia will be assumed at least after 60 seconds in the presence of stable systemic blood pressure decrease compared to baseline remaining for at least 10 heart-beats. In case of intracoronary infusion, incremental boli of intracoronary adenosine (60, 300 and 600 μg) will be administered with each next dose given at least 60 seconds apart, or after returning to baseline hemodynamic conditions. Each administration will be performed within 5 to 10 seconds and rapidly flushed by saline solution. The following higher dose will not be administered in the case of an atrio-ventricular block lasting more than 5 seconds. In such cases, intravenous adenosine will be used to induce maximal hyperemia [17]. Similarly, in the case of FFR values between 0.81 and 0.83 with 600 μg intracoroary adenosine, FFR will be retested using intravenous adenosine [17]. Finally, an FFR value of ≤0.80 will be considered abnormal. When more than one stenosis is present in the same artery, a pull-back maneuver under maximal hyperemia to determine the exact location and physiological significance of sequential stenosis will be adopted.

If an FFR value of >0.80 is measured on the target AICL, patients will be treated with optimal medical therapy only. If an FFR of ≤0.80 is obtained, patients will undergo a FFR-guided PCI. This means that the patient will undergo conventional PCI with stenting of the AICL in order to achieve a post-stenting FFR ≥0.90. If post-stenting FFR is <0.90 a further post-dilation of the stent will be performed, and if FFR remains at <0.90, a pull-back of the wire to identify another possible pressure drop and/or a subsequent stent implantation at least 5 mm from the stent will be performed according to physician’s preference.

